**Abstract:**

Most HIV-1 infected individuals in areas of high seroprevalence live in crowded urban settings. These conditions are associated with repeated helminth infections, which may alter immune function increasing the susceptibility and severity of other infections in these individuals. Prior observational studies have shown that in HIV-1 infected individuals, helminth infections are associated with immune activation and increased HIV-1 RNA levels. It is important to determine whether treating helminth co-infection in patients with HIV-1 will slow disease progression or reduce transmission.

We plan to determine the prevalence of helminth infection in HIV infected adults, characterize the short-term effect of antihelminth therapy on HIV-1 disease progression and immune activation markers, and examine co-factors for helminth infection, such as CD4 count, viral load, age, gender and duration of time spent in an urban setting. In addition, we will conduct a randomized clinical trial to determine the effect of helminth eradication on markers of immune activation and HIV-1 disease progression and transmissibility. The study will be conducted in a group of HIV-1 infected individuals who do not yet meet criteria for HAART. Identifying inexpensive and practical methods to delay HIV-1 progression offers tremendous public health benefits. At the present time, highly active antiretroviral therapy is being rapidly scaled up in resource poor settings. The demand for these drugs currently far outweighs the capacity for such services to be provided in many regions. For the millions of people affected and infected by HIV-1 in resource poor settings, delaying immunosuppression for months to years could allow important developments in infrastructure that would permit the maximum number of individuals to benefit from highly active antiretroviral therapy. In addition, it is important to identify inexpensive and effective methods to reduce HIV-1 transmission.

**Introduction and Background:**

Of the approximately 25 million HIV-1 infected individuals currently living in Africa, as many as 50-90% may be co-infected with soil transmitted helminths such as roundworms, hookworms or whipworms. Several studies examining the effect of helminth co-infection on individuals infected with HIV-1 suggest that these helminth co-infections may increase HIV-1 viral load and may lead to more rapid progression of HIV-1 disease. In many resource-poor settings, HIV-1 treatment programs are being rapidly scaled up to provide antiretroviral therapy to immunosuppressed HIV-1 infected individuals. These programs offer significant potential benefit to the millions of infected individuals who currently meet treatment criteria. However, additional strategies must be developed in order to delay immunosuppression and antiretroviral initiation for the majority of infected individuals who do not yet meet criteria for treatment (CD4 count  $\geq 200$  cells/mm^3). Delaying immunosuppression among HIV-1 infected individuals promises to spare antiretroviral toxicity, conserve the limited repertoire of antiretroviral options, and to prolong survival. Co-infection prophylaxis merits evaluation because it may provide an effective and relatively inexpensive means to delay immunosuppression in these individuals.

Helminth infection leads to significant stimulation of the host immune response. These infections are often characterized by the daily production of millions of eggs, excretory products, and secretions that result in a state of persistent activation of the host immune system. Specifically, helminth infected individuals display increased levels of eosinophilia, increased IgE levels, and a Th2 immune bias. The effects of such immune activation are not entirely clear, but several studies have suggested that this increased activation of the Th2 immune subset may further enhance HIV replication and progression. In addition, the enhanced Th2 response seen in these infections may have a detrimental effect on the host's

ability to respond to other infections, particularly those dependent on Th1 immune responses, such as tuberculosis.

In an Ethiopian study of HIV-1 infected and uninfected individuals, helminth infections resulted in increased memory CD4 cells and increased T-cell activation, and treatment of helminth infections was associated with decreased T-cell activation. Interestingly, among the HIV-1 infected individuals in this observational study, treatment of helminth infection resulted in a significant increase in absolute CD4 counts (192 versus 279 cells/mm^3,  $p=0.002$ ). In another study of 56 HIV-1 infected individuals in Ethiopia, 31 (55%) had helminth co-infections with one or more species detected in stool samples, mainly *Ascaris lumbricoides* and *Trichuris trichiura*. At baseline, there was a strong association between stool helminth burden and plasma HIV-1 RNA levels among individuals with helminth co-infection ( $p<0.001$ ). In addition, successful treatment of co-infection (as documented by clearance of helminth eggs in stool) led to a significant decrease in HIV-1 plasma viral load ( $-0.36 \log_{10}$ ) in these patients. This change in viral load was significantly greater than that seen in those individuals without documented clearance of their helminth co-infection ( $+0.67 \log_{10}$ ) ( $p=0.04$ ). Other studies suggest that this effect may be variable, depending both on the type and duration of helminth co-infection as well as on host immune status. In one such study from Kenya, plasma HIV-1 RNA levels did not decrease significantly following treatment of schistosomiasis.

The majority of HIV-1 infected individuals do not yet meet criteria for HAART. These individuals continue to transmit the virus and perpetuate the epidemic. For each log increase in plasma HIV-1 viral load, there is an estimated 2.5-fold increased risk for transmission to the sexual partner of the infected individual. Thus, the benefit of reducing viral load by even 0.5 log could be substantial. Identifying inexpensive and feasible interventions that may reduce viral load has the potential for significant public health benefit.

### **Justification of the Study:**

To date, there are no randomized clinical trials evaluating the effect of anti-helminth treatment on immune activation, CD4 count, and HIV-1 viral levels. It is important to determine whether routine treatment of helminth co-infection should be considered standard practice in the treatment of HIV-1 infected individuals in helminth endemic areas. Such treatment may be a useful strategy to delay HIV-1 progression and prevent transmission of HIV-1 among individuals in resource-poor settings. Interval anti-helminth therapy may be a feasible option in many areas of the world to delay immunosuppression, to enhance the response to antiretroviral therapy or to reduce infectiousness in HIV-1 infected individuals. In addition, as patients progress to HAART, it is important to determine the ideal timing for helminth eradication.

**Hypothesis:** Treatment of gastrointestinal helminths in patients with HIV-1 may impact markers of disease progression and infectiousness, namely CD4 count and plasma and genital HIV-1 RNA levels, when compared to no treatment in these individuals.

### **Overall General Objectives:**

To evaluate the effect of helminth co-infection on HIV-1 disease progression and transmission in a cohort of HIV-1 infected Kenyan adults who do not meet criteria for highly active antiretroviral therapy.

### **Specific Objectives:**

1. To determine prevalence and correlates of helminth co-infection in HIV-1 infected individuals in various clinics in or around Nairobi, Kenya. Baseline demographic, socio-economic and geographic data such as age, gender, income, education, occupation and place of residence will be collected and compared to determine what factors influence the prevalence of helminth infection in patients with HIV-1.
2. To determine if treatment of intestinal helminths in HIV-1 infected adults can delay disease progression, as measured by CD4 counts and HIV-1 RNA viral loads.
3. To determine if treatment of intestinal helminths in HIV-1 infected adults can reduce shedding of genital HIV-1 and impact transmission.

## DESIGNS AND METHODOLOGY

### Study Site

The study will be conducted in Nairobi, Kenya. The University of Washington has a history of collaborative research with the Kenya Medical Research Institute, the University of Nairobi, and Kenyatta National Hospital; all leading academic institutions in Kenya. Enrollment in the randomized clinical trial will take place in several clinics in Kenya which may include clinics in Kibera, the KNH Comprehensive Care Clinic, KEMRI, Kiambu District Hospital, Homa Bay, Kerugoya, Coptic Hope Clinic, Mbagathi District Hospital, Thika District Hospital, and The Comprehensive Care and Research Clinic at Kilifi District Hospital (CGMR-C).

### Study Populations

Individuals who are 18 years or older, who plan to reside within 25 kilometers of the study clinic site for at least 3 months after initiation of treatment and who are interested in study participation will be enrolled after written informed consent is obtained. Subjects must also meet the following inclusion/exclusion criteria;

#### *Inclusion Criteria*

- Participants must not be or have been on highly active antiretroviral therapy.
- Participants must have CD4 count  $>250$  cells/mm^3 in order to be enrolled in the randomized controlled trial. Patients with lower CD4 counts may be screened but will not be randomized.
- Participants must be at least 18 years of age.
- Participants must be able and willing to participate and give written informed consent.
- Participants must be able and willing to return for the scheduled follow-up visits
- In addition, in order to be included in the treatment phase of the study, patients must have at least one stool specimen positive for a soil transmitted helminth.

#### *Exclusion Criteria*

- Participants who have received treatment for helminth infection in the past 6 months (by self report or chart review)
- Participants must not be pregnant at the time of treatment (by urine HCG testing).
- Participants who present with other serious co-morbidities such as severe anaemia, malaria or tuberculosis

### Sample Size

Sample size determination – Assuming a power of 80% and alpha of 0.05, we have calculated that 100 individuals would be needed in each arm to detect a difference in CD4 count of 40 cells/mm^3 following anti-helminth therapy (SD of 200 cells/mm^3).

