### Procedures

*Summary:* This study will be conducted in two phases. Initially, 20 HIV-1 infected patients from each of several clinic sites will be screened by stool microscopy for the presence of helminth co-infection. These data will be used to determine the prevalence of infection at various sites and to compare baseline variables between groups as described above. These data will also help determine which study site will likely provide a population with sufficiently high prevalence in which to conduct the second phase of the study. This second phase will be a randomized double blind, placebo controlled clinical trial of anti-helminth treatment among HIV-1 and helminth infected adults. All patients will receive therapy for helminth infection either immediately or deferred (at twelve weeks post enrolment). As patients will be screened at enrolment for helminth infection, total prevalence will be calculated and determined for the entire screened population.

*Pilot study to identify optimal trial site:* Initially, we will conduct a pilot study to determine the prevalence of helminth co-infection in HIV-1 infected individuals in several clinic sites at different locations in or around Nairobi and some potentially in more rural sites elsewhere in Kenya. Twenty HIV-1 infected individuals will be enrolled at each clinic site and fresh stool obtained for microscopy. Individuals with helminth infections will either be offered enrolment in the treatment phase of the study described below (if proximate to the proposed site of the clinical trial study) or treated with open label albendazole 400 mg a day for three days and referred back to the clinic in which they receive regular care.

The study site that is the most feasible for the trial will be selected based on the data from the pilot study (specific aim 1) to be the base for larger scale screening to identify 200 HIV-1 infected helminth co-infected individuals. Specific factors that will be considered for site selection include helminth prevalence and ability to recruit HIV-1 infected helminth co-infected individuals. Depending on helminth prevalence this may require screening ~600 to 2000 individuals (10% to 30% estimated helminth prevalence).

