### Laboratory

*CD4 measurement* will be assessed by FACSCalibur in Nairobi, Kenya.

*Stool microscopy* will be performed by technicians with training and certification in the differentiation and quantification of stool helminth species. Testing will be done using conventional microscopic techniques.

*HIV-1 RNA levels* will be quantified at the [name]'s laboratory at Fred Hutchinson Cancer Research Center in Seattle. Below is an explanation of the reasons for preference of this laboratory site:

1. Research collaborations have involved long-standing relationships with the University of Nairobi, KEMRI, and KNH, and University of Washington and the Fred Hutchinson Cancer Research Center. This collaboration has conducted studies in HIV infected individuals in Kenya for many years. HIV-1 RNA assays for these studies have been done at the laboratory of [name] in Seattle, USA. Dr.

[name] has made significant efforts to transfer technology for HIV-1 DNA filter paper assays and HIV-1 RNA assays for research studies. We are optimistic that DNA filter paper assays and potentially HIV-1 resistance assays will be conducted in Nairobi within 2 years.

2. Over the past many years, [name] laboratory has taken care to delineate subtype-related issues to optimize measurement of HIV-1 RNA in Kenya with a non-commercial Gen-Probe TMA (transcription-mediated assay) specifically tailored for subtypes A, D, and C from Kenyan isolates. Thus, it is useful to correlate the proposed study to other large-scale studies in Nairobi conducted by our research team.
3. Available funding for this study will not be sufficient to measure viral RNA in even 60 individuals at 2 time-points if these measurements were done locally (cost per assay in Nairobi ~4-5 times the cost at [name] laboratory). Under the current budget constraints we would likely be limited to a small subgroup analysis of 30 patients.

Given the improved design of the study with an increased sample size including 200 individuals, measuring HIV-1 RNA in all participants would significantly strengthen the study and increase the potential that significant effects on viral decline would be found.

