### *Data Management*

*Data Entry and Storage:* All data will be collected on preprinted forms that are able to be scanned directly or data entered into a software data management program (Teleform SPSS or ACCESS). Data will be collected at enrollment and at each follow up visit on these forms. Following collection, the data forms will be scanned into the database as described above. Original data forms will be stored in the study offices with access restricted to study investigators. Following completion of all data collection, the data forms will be archived. At 1-year following completion of the study, identifiers will be removed from the data. Data will be the property of KEMRI and the University of Washington.

*Data verification:* A data clerk from KEMRI will be employed to hand verify that all data is completed accurately and that the computerized scanned data is comparable to the paper forms. Data will be cleaned by the Fellow Investigator and the data clerk and at that time a second verification of accuracy will be performed.

*Data Analysis:*

**Aim 1:** Prevalence of helminth co-infection will be determined in the total screened population by individual, by clinic and by cohort. To determine correlates of helminth co-infection, mean CD4 count, age and log10 RNA levels will be compared in individuals with and without helminth co-infections using t-tests. Dichotomous variables (socio-demographic) will be compared with Chi square tests in individuals with and without helminth co-infection. Similar analyses will be conducted to determine correlates of re-infection and eradication.

**Aim 2:** All analyses will be intent-to-treat. To assess the success of randomization we will compare baseline characteristics between the 2 randomization groups. To determine the effect of antihelminth treatment on disease progression markers, we will compare month one measurements of mean CD4 count, log10 plasma HIV-1 RNA, and percentage of cells with specified immune activation markers in the 2 study arms using t-tests or non-parametric testing. In addition, prevalence of helminth co-infection will be compared in the 2 study arms using Chi-square tests. To determine the effect of antihelminth treatment on infectivity, we will compare enrollment measurements of mean genital HIV-1 RNA levels with the 12 week follow up measurements.

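### 100 per arm gives about 29% power, not 80%, for a 40-cell CD4 difference with SD 200

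*Protocol*

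**What the plan says.** All the inputs stand in the one sentence of the Sample Size section. It begins "Assuming a power of 80% and alpha of 0.05", continues "we have calculated that 100 individuals would be needed in each arm to detect a difference in CD4 count of 40" cells/mm³, and gives the variability as "SD of 200 cells/mm"³. It does not say whether alpha is one- or two-sided, whether the SD is that of a single CD4 count or of a change, or which formula was used. It makes no allowance for loss to follow-up.

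The Procedures section carries the number forward as "larger scale screening to identify 200 HIV-1 infected helminth co-infected individuals".

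The analysis is given under Data Management, Data Analysis, Aim 2. Mean follow-up CD4 count is compared "in the 2 study arms using t-tests or non-parametric testing". Part b of the Clinical Trial section has CD4 measured at baseline as well, but Aim 2 mentions no change score and no adjustment for the baseline value.

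**The concern.** A 40-cell difference with an SD of 200 is a standardised difference of 0.20, which is small. A two-arm comparison of means normally needs several hundred per arm to detect an effect of that size, so 100 per arm with 80% power does not look possible.

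The sentence matters because CD4 count is the only outcome with a sample size justification, and it is one of the two markers named in Specific Objective 2. If power is about 29%, a true 40-cell effect would be missed about seven times in ten. Anyone judging a non-significant result against a claimed 80% power would give it more weight than it deserves. The section on expected application of the results says that the data will feed the sample size of a larger trial, so the same slip could be carried over.

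**Working it through.** **Inputs.** Difference 40, SD 200, alpha 0.05, power 80%, 100 per arm (all from Sample Size); comparison of two arm means, unadjusted (Data Analysis, Aim 2). Two-sided testing is assumed as the convention, and one-sided testing is also shown.

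**1. Try to reproduce 100 per arm.**

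n per arm = 2(z₀.₉₇₅ + z₀.₈₀)² / (40/200)² = 2 × 7.849 / 0.04 = 392.4, so 393 by the normal approximation. The exact t-test gives 393.4, so 394 per arm (788 in total).

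One-sided at 0.05: 310 per arm.

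The stated 100 is not reproduced either way.

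**2. Power at 100 per arm.**

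Standard error = 200 × √(2/100) = 28.28. 40/28.28 = 1.414.

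- Two-sided: Φ(1.414 − 1.960) = Φ(−0.546) = 29.3%; exact t-test 29.1%.
- One-sided: Φ(1.414 − 1.645) = Φ(−0.231) = 40.9%; exact t-test 40.7%.

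**3. Difference detectable with 80% power at 100 per arm.**

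(1.960 + 0.842) × 28.28 = 79.2 cells/mm³; exact t-test 79.6.

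**4. What would give about 100 per arm?**

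| Change to the stated inputs | Result |
|---|---|
| SD about 100 instead of 200 | 99 per arm with SD 100 |
| Difference 80 instead of 40 | 99 per arm |
| One-sample (paired) formula: 7.849/0.04 = 196.2, t-based 198.2 | about 198 in total, or about 100 per arm if split over two arms |
| SD 200 cross-sectional, analysis adjusted for baseline (ANCOVA) | needs r = √(1 − (100.96/200)²) = 0.86 |
| SD 200 cross-sectional, analysis of change | needs r = 1 − (100.96/200)²/2 = 0.87 |

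Here 100.96 is the SD at which 100 per arm has 80% power: 40 / (2.802 × √(2/100)). None of these inputs is in the protocol. If 200 is instead the SD of the change, a two-arm comparison of changes still has 29% power.

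**5. Baseline adjustment over assumed correlations** (SD 200 taken as cross-sectional, 100 per arm, normal approximation for power).

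| Assumed r | ANCOVA power for 40 cells | Detectable difference, 79.6 × √(1 − r²) |
|---|---|---|
| 0.5 | 37% | 69 |
| 0.7 | 51% | 57 |
| 0.8 | 65% | 48 |

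**6. Width of the confidence interval.**

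Unadjusted, SD 200, 100 per arm: half-width of the 95% interval is about 1.97 × 28.28 = 55.8 cells/mm³. An estimate below 40 − 55.8 = −15.8 would exclude a benefit of 40. If the true effect were zero, that would happen with probability Φ(−15.8/28.28), about 29%.

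**7. Loss to follow-up.** With an assumed 10% loss (90 per arm), power for 40 cells falls to about 27% and the detectable difference rises to about 84.

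**The case against.** The best defence is that baseline CD4 is collected, so a more efficient analysis was available and the sponsor may have had it in mind. That would help, but Aim 2 does not specify it, and the claim would then hold only at a correlation of about 0.86 or more, which is not stated. Nor does the unstated sidedness rescue the figure, since a one-sided test gives about 41%. The non-parametric alternative named in Aim 2 is not a plausible way to close a nearly fourfold gap in sample size.

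A second defence is that the study presents itself as groundwork for a larger trial and also analyses plasma HIV-1 RNA and immune activation markers. This is fair and softens the consequence. It leaves the power statement as wrong as before.

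Two stronger readings are tempting and should not be adopted.

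- A reader might infer that the figure must come from a one-sample formula whose total was then divided between two arms. The arithmetic fits, but a halved SD, a doubled difference or an unstated baseline correlation fits as well. The protocol gives no formula, so the origin is unknown.
- A reader might infer that the design can never exclude a 40-cell effect. Step 6 shows otherwise: an estimate below about −16 would exclude it. What is excluded depends on the interval observed. Nor does the protocol say that a null result would be read as evidence against 40 cells; that is a risk created by the power claim, not a stated plan.

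**Conclusion.** The power statement is wrong as written. With the protocol's own difference, SD, alpha and number per arm, and the two-arm comparison it plans, power is about 29% two-sided (about 41% one-sided) instead of 80%. The number needed for 80% is about 394 per arm, nearly four times the plan, and the planned 200 participants can detect about 80 cells/mm³.

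These figures take the SD of 200 at face value, equal arms, complete follow-up and no baseline adjustment. The first is the one most open to doubt: if 200 is a misstatement for an SD near 100, the sample size is right and the SD is the error. Only the sponsor can settle that. As the text stands, the inputs and the result cannot all be true.

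**What to change.** First, state in the Sample Size section what the SD of 200 refers to (a single CD4 count or a change), the test, and the sidedness. Then reconcile the paragraph.

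- **If SD 200 stands and the analysis is unadjusted:** keep 200 participants and restate along these lines: *With 100 per arm and an SD of 200 cells/mm³, a two-sided t-test at 0.05 has 80% power to detect a difference of about 80 cells/mm³ and about 29% power for 40 cells/mm³.*
- **If an analysis adjusted for baseline CD4 is specified instead:** name it under Aim 2, and give the assumed correlation and the resulting detectable difference (for example about 57 cells/mm³ at an assumed r of 0.7 and about 48 at 0.8).

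In either case add a sentence on interpretation: a non-significant CD4 result will be interpreted from its confidence interval (expected 95% half-width about 56 cells/mm³ without adjustment) and will not by itself be taken as evidence against a 40-cell effect.

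**Cost.** Restating the paragraph needs no extra participants and no new data collection. The price is a less favourable detectable difference, and the sponsor must be content that a trial aimed at about 80 cells (or about 50 to 60 with adjustment) is still worth doing. If 80% power for 40 cells must be kept with SD 200 and no adjustment, wording will not deliver it. About 788 co-infected participants would be needed, which at the protocol's prevalence range of 30% to 10% means screening roughly 788/0.30 = 2,600 to 788/0.10 = 7,900 people.
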